## Abstract

The Belgian Diabetes in Pregnancy follow-up study (BEDIP-FUS) aims to investigate the impact of body mass index (BMI), adiposity and different degrees of glucose intolerance on the metabolic profile and future risk for type 2 diabetes (T2D) in women and offspring five years after delivery in the BEDIP study. The BEDIP study was a prospective cohort study to evaluate different screening strategies for gestational diabetes (GDM) based on the 2013 WHO criteria. The aim of the BEDIP-FUS is to recruit 375 women–offspring pairs, stratified according to three different subgroups based on the antenatal result of the glucose challenge test (GCT) and oral glucose tolerance test (OGTT) during the BEDIP pregnancy. The follow-up visit consists of a 75 g OGTT, anthropometric measurements and questionnaires for the mothers, and a fasting blood sample with anthropometric measurements for the child. Primary outcome for the mother is glucose intolerance defined by the American Diabetes Association criteria and for the offspring the BMI z-score. Recruitment began in January 2021. The BEDIP-FUS study will help to better individualize follow-up in women with different degrees of hyperglycemia in pregnancy and their offspring.

## 1. Introduction

Gestational diabetes mellitus (GDM) is described as diabetes first diagnosed during pregnancy provided that overt diabetes in early pregnancy has been excluded [1].Women with GDM have a seven-fold increased risk of developing type 2 diabetes (T2D) later in life compared to normal glucose tolerant (NGT) pregnant women [2,3]. After delivery, the underlying β-cell dysfunction and/or predisposing insulin resistance generally persist and are associated with the severity of glucose intolerance at the time of pregnancy [4]. Women with persistent glucose intolerance (impaired fasting glucose (IFG) and/or impaired glucose tolerance (IGT)) in early postpartum are a particularly high-risk group, with approximately one in two developing T2D within five years postpartum [5]. Women with GDM have a significantly higher risk of developing metabolic syndrome and cardiovascular disease, compared to normal glucose tolerant women [6,7]. Stratifying subgroups with a differential risk of developing an adverse cardiometabolic profile later in life offers a chance to better individualize the follow-up, management and prevention in this metabolic high-risk population. A Canadian postpartum follow-up study of different gestational glucose tolerance groups, based on the antenatal glucose challenge test (GCT) and 100 g oral glucose tolerance test (OGTT) using the National Diabetes Data Group criteria, showed that each degree of gestational glucose intolerance predicts distinct trajectories of β-cell function, insulin sensitivity and glycemia in the first three years postpartum which drive the differential risk of future T2D [4]. However, only limited data are available on the long-term risk of developing T2D in women with GDM diagnosed by the one-step approach and 2013 WHO criteria. Studies have shown that 30–50% of women with GDM develop T2D within the first 10 years after the index pregnancy before the introduction of the 2013 WHO screening [2]. An Irish study showed a rate of (pre)diabetes of 26% up to five years post-delivery in women with GDM diagnosed using the universal one-step approach and 2013 WHO criteria [8,9]. Additionally, we have demonstrated that gestational glucose tolerance worsens from normal to mildly abnormal (abnormal GCT but normal OGTT) to GDM in the BEDIP-N study based on a GCT ≥ 130 mg/dL and 75 g OGTT using the 2013 WHO criteria [10]. The future risk of developing T2D might gradually increase across these different glucose tolerance groups.

Additionally, screening tests such as the OGTT are time-consuming and uncomfortable, and they have limited reproducibility. Novel biomarkers that can adequately predict T2D after GDM are, therefore, needed. In diabetes, glycated CD59 is formed by non-enzymatic glycation which inactivates the complement inhibitor CD59. The research group of [name] (Hematology lab Harvard) has demonstrated that by using a sensitive and specific enzyme-linked immunosorbent assay (ELISA) for glycated CD59 in blood, plasma glycated CD59 levels were significantly higher in individuals with T2D and independently predicted the response to the OGTT [11]. Glycated CD59 has also been shown to be a promising predictor for GDM and LGA [12]. We have previously shown that plasma glycated CD59 has a high negative predictive value in determining which women could avoid an OGTT in early postpartum [13]. We plan, therefore, to analyze glycated CD59 as a potential biomarker to predict the long-term metabolic risk for women with previous GDM and their offspring.

Offspring of women with GDM have an increased risk of becoming obese and develop T2D during their life [14,15]. Most human studies showing a relationship between in utero exposure to hyperglycemia and the occurrence of obesity and diabetes in the offspring have not investigated important confounders such as maternal and paternal obesity, socio-economic status and lifestyle behavior [16]. Increased maternal BMI is associated with increased childhood adiposity via mutual genetics, familial behavior, environmental aspects and the intrauterine setting [16]. Several studies have shown that adjusting for maternal BMI attenuates the associations between GDM and childhood obesity [17]. The follow-up of the HAPO study (HAPO-FUS) showed that among children of mothers with GDM based on the 2013 WHO criteria compared to those without GDM, the difference in childhood overweight and obesity defined by BMI was not statistically significant after adjustment for maternal BMI [18]. The HAPO-FUS study showed that, in children aged 10–14 years, there was an association between exposure to higher levels of glucose in utero and childhood glucose and insulin resistance, and this was independent of maternal and childhood BMI and family history of diabetes [19]. A Danish study evaluating the offspring of GDM mothers showed that, after correction for offspring BMI and maternal pre-pregnancy BMI, the offspring of women with GDM still had significantly higher fasting glucose, insulin resistance and waist-to-hip ratio compared to offspring of women without GDM [15]. By stratifying the results according to pre-pregnancy BMI, this study also suggests that hyperglycemia may be more significant in the absence of severe maternal adiposity [15].

More research is needed that determine the long-term metabolic risk of women and their offspring across different gestational glucose intolerance groups based on the 2013 WHO criteria. Therefore, we hypothesize in the BEDIP-FUS study that each degree of gestational glucose intolerance based on the antenatal GCT and OGTT with the 2013 WHO criteria predicts distinct postpartum trajectories of weight, β-cell function, insulin sensitivity and glycaemia in both women and offspring. In general, this research answers the need to better stratify women and offspring across different degrees of gestational glucose intolerance for their risk of developing an adverse cardiometabolic profile later in life. We hypothesize that the results of this research will help to optimize the follow-up, prevention and treatment of women with a previous history of different degrees of hyperglycemia in pregnancy.

## 2. Aim and Objectives of the BEDIP-FUS Study

We aim to investigate the impact of BMI, adiposity and different degrees of glucose intolerance on the metabolic profile and future risk for T2D in women and offspring across different gestational glucose tolerance groups on average five years after delivery in the BEDIP-N study. Additionally, we plan to evaluate the novel biomarker glycated CD59 to predict the long-term cardiometabolic profile in mothers and offspring.

To achieve this, the following specific objectives will be addressed in women and offspring across different gestational glucose tolerance groups on average five years after delivery:The prevalence of glucose intolerance (T2D and prediabetes);The prevalence of overweight and obesity;The degree of adiposity;The prevalence of metabolic syndrome;The degree of insulin resistance;The degree of β-cell dysfunction;Glycated CD59 as a predictor of metabolic dysfunction;Sex differences in metabolic profile in the offspring.

## 3. Methods and Analysis

### 3.1. Study Design and Setting

This is a Belgian multi-centric prospective follow-up study of the BEDIP-N cohort (Figure 1). The BEDIP-N study was a multicentric prospective cohort study to compare different screening strategies for GDM, which has been previously described in detail [10,20,21,22]. In this follow-up study, five of the original seven centers are participating (University hospital of Leuven (UZ Leuven), Antwerp University Hospital, OLVZ-Aalst, OLVZ-Asse and Imelda Bonheiden). UZ Leuven is the coordinating center. Of all participants in the BEDIP study, 95% consented to be contacted within 10 years after the study end to potentially participate in a follow-up study. Women who consented to be contacted, are invited by email, phone or letter to participate in the BEDIP-FUS study. Our study is registered in ClinicalTrials.gov as NCT04429958 since June 2020 and was approved by the Medical Ethical Committees of all participating centers.

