### 3.2. Recruitment and Eligibility

We aim to recruit 375 women–offspring pairs with the five largest centers who participated in the initial BEDIP study, which is approximately 21% of the initial 1800 women who received both a GCT and 75 g OGTT in the BEDIP study. Women and offspring are recruited according to three different subgroups based on the antenatal result of the GCT and OGTT in the index pregnancy (a sample of 125 in each group): GDM group; NGT on the OGTT with an abnormal preceding GCT (abnormal GCT-NGT group); NGT on the OGTT with a normal preceding GCT (normal GCT-NGT group). Abnormal GCT is defined as glucose ≥ 130 mg/dL, as we have previously shown to have an acceptable sensitivity to screen for GDM in our population (20). Additional analyses will be performed on the different subgroups stratified by a GCT ≥ 140 mg/dL to evaluate whether this leads to more pronounced differences in β-cell function and insulin sensitivity across the different groups. GDM was defined by the 2013 WHO criteria. Recruitment began in January 2021 and will end around December 2023.

Eligibility criteria:

The inclusion criteria for the mother are:Age ≥ 18 years;Participated in the completed BEDIP-N study and received both the GCT and the OGTT during pregnancy;

The inclusion criterion for the offspring is:Born at the time of participation in the BEDIP-N study.

The inclusion criterion for the father is:Biological father of the child born during participation in the BEDIP-N study.

The exclusion criteria for the mother are:Current pregnancy;Current treatment that influences glycemic status, such as high dose corticoids or incretin mimetic medication;History of bariatric surgery or any gastrointestinal surgery that alters glucose absorption (Billroth II);Inability to complete a normal study visit (incompliance, psychiatric problems);Diagnosis of type 1 diabetes or the presence of autoimmune antibodies for type 1 diabetes.

The exclusion criteria for the offspring are:Current treatment that influences glycemic status, such as high dose corticoids;Inability to complete a normal study visit (incompliance, psychiatric problems);Diagnosis of type 1 diabetes or the presence of autoimmune antibodies for type 1 diabetes.

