### 3.6. Power Calculation and Statistical Analyses

#### 3.6.1. Sample Size

Since there are currently no data on the long-term metabolic risk of lesser degrees of hyperglycemia than GDM based on the GCT and 75 g OGTT using the currently recommended 2013 WHO criteria, we based our power calculation on the Canadian study by Ravi Retnakaran et al. in which women received the GCT and 100 g OGTT using the National Diabetes Data Group criteria [4]. The distribution of the patients over the groups was based on the BEDIP-N study as previously published [10]. The power calculation is performed for the primary outcome for mothers: glucose intolerance after on average five years. We aim to compare glucose intolerance as a binary outcome variable between the GDM group (3), where a 26% prevalence is assumed, and (1) normal GCT-NGT group and (2) abnormal GCT-NGT group, with an assumed prevalence of 4% and 12%, respectively, with 125 subjects in each group. Considering a chi-square test, the power for the comparisons of the primary outcome at a 5% significance level, is 99% (1 vs. 3) and 81% (2 vs. 3), respectively.

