Studies provide no evidence yet that treating GDM in pregnancy can reduce the future risk for obesity and glucose intolerance in mothers and offspring. Reduction of macrosomia at birth was seen in women with GDM who received intensified glucose-lowering treatment, but follow-up studies of offspring showed no decline in childhood obesity or metabolic dysfunction in these children at the age of 4–10 years [42,43]. However, in an American study, sex-specific differences were seen, with a decreased frequency of impaired fasting glucose, lower fasting glucose, and lower insulin resistance in female offspring but not in male offspring [43]. Differing sensitivities to hyperglycemia in utero may result in long-term sex-specific programming. Additional studies are needed to understand the separate role and the combined potential superimposing effect of maternal hyperglycemia, maternal obesity during pregnancy and paternal BMI on the metabolic health of offspring. Moreover, data on the metabolic profile of offspring of women diagnosed with GDM according to the 2013 WHO criteria are scarce. Studies should also investigate sex differences in metabolic profiles in the offspring. With the BEDIP-N follow-up study we aim, therefore, to also evaluate potential sex differences in long-term metabolic risk across different gestational glucose tolerance groups in pregnancy.

A major strength of our study is that all women received both a GCT as well as an OGTT during pregnancy, allowing investigation of the impact of different glucose tolerance groups during pregnancy on the long-term glucometabolic risk of women and their offspring. We also have a large dataset on pregnancy and delivery outcomes for both mother and offspring. A limitation of our study is that our cohort mainly consists of Caucasian women.

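### Voluntary attendance into equal quotas: the described analysis takes no account of participation or of the quota mix, which exposes the group prevalences and the pooled GDM versus non-GDM contrast

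*Protocol article*

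**What the plan says.** All of this is in the protocol article.

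- **Objective (section 2).** The first item listed, to be addressed across the gestational glucose tolerance groups, is "The prevalence of glucose intolerance (T2D and prediabetes".
- **Route in (section 3.1).** Of the BEDIP participants, "95% consented to be contacted within 10 years after the study end". Then: "Women who consented to be contacted, are invited by email, phone or letter to participate in the BEDIP-FUS study". Five of the original seven centers take part.
- **Quotas (section 3.2).** The target is 375 pairs, "which is approximately 21% of the initial 1800 women who received both a GCT and 75 g OGTT in the BEDIP study", split as "a sample of 125 in each group".
- **Planning values (section 3.6.1).** The comparison is "between the GDM group (3), where a 26% prevalence is assumed" and the two NGT groups, "with an assumed prevalence of 4% and 12%, respectively, with 125 subjects in each group". The 4% belongs to the normal GCT-NGT group and the 12% to the abnormal GCT-NGT group.
- **Analysis (section 3.6.2).** Linear and logistic models compare GDM with non-GDM and, separately, the three groups. Adjustment has three steps. A variable qualifies if it is linked to both group and outcome. Participation, sampling fractions and weights are not mentioned.
- **Data held (section 4).** "We also have a large dataset on pregnancy and delivery outcomes for both mother and offspring"

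**The concern.** The follow-up sample is not a random draw from each BEDIP-N group. It consists of women who chose to come for a fasting OGTT and bring a fasting child, and the group sizes are set by the design. This raises two issues.

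1. **Participation.** If women at higher glycaemic risk are more or less willing to attend, the proportion affected among attenders is not the proportion affected in the group they came from. Covariates in a regression fitted to attenders give conditional contrasts; they do not recover the group's prevalence. The rule for choosing covariates does not ask whether a variable predicts attendance.
2. **Quota mix.** The pooled GDM versus non-GDM contrast merges two NGT groups whose assumed prevalences differ threefold (4% and 12%). Equal quotas fix their mix at 50:50 whatever it is in the cohort. This needs no self-selection at all.

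At stake are the headline prevalences, which are meant to inform follow-up after pregnancy, and the pooled odds ratio.

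**Working it through.** **Inputs.** From section 3.6.1: prevalences 4%, 12% and 26%, with 125 per group. From sections 3.1 and 3.2: 375, 1800 and 95%. The attendance ratio r and the cohort mix of the NGT groups are not in the document; both are assumptions, shown as ranges.

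**1. The plan's own figures.** Power of the two-sided 5% chi-square test (normal approximation, pooled variance under the null) is Φ[(d − 1.96·SE₀)/SE₁].
- 12% vs 26%: d = 0.14; SE₀ = √(2·0.19·0.81/125) = 0.0496; SE₁ = √((0.12·0.88 + 0.26·0.74)/125) = 0.0488. Power = 80.9% (stated 81%).
- 4% vs 26%: the same formula gives 99.9% (stated 99%).

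The planning values can therefore be used as they stand. The sampling target is 375/1800 = 20.8%, or 375/(0.95·1800) = 21.9% if the 95% consent rate is applied to the 1800.

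**2. Effect of attendance.** Let r = P(attend | glucose intolerant) / P(attend | not intolerant) within a group. Then:
- observed prevalence = p·r / (p·r + 1 − p), so the prevalence odds are multiplied by r;
- observed odds ratio = true odds ratio × (r in GDM group / r in comparator).

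True odds ratio, GDM vs abnormal GCT-NGT: (0.26/0.74)/(0.12/0.88) = 2.58.

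| r | GDM prevalence observed (true 26%) | OR if r acts in the GDM group only | OR if r is equal in all groups |
|---|---|---|---|
| 0.75 | 0.195/0.935 = 20.9% | 1.93 | 2.58 |
| 1.25 | 0.325/1.065 = 30.5% | 3.22 | 2.58 |
| 1.5 | 0.390/1.130 = 34.5% | 3.86 | 2.58 |

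Even when r is equal everywhere and the odds ratio is untouched, every prevalence moves. At r = 1.5 the abnormal GCT-NGT group goes from 12% to 0.18/1.06 = 17.0%, and the normal GCT-NGT group from 4% to 0.06/1.02 = 5.9%.

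**3. Effect of the quota mix.** Let w be the share of normal-GCT women among non-GDM women. Non-GDM prevalence = 0.04w + 0.12(1 − w), and GDM odds = 0.26/0.74 = 0.351.

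| w | Non-GDM prevalence | OR, GDM vs non-GDM |
|---|---|---|
| 0.5 (quotas) | 8.0% | 4.04 |
| 0.6 (assumed) | 7.2% | 4.53 |
| 0.7 (assumed) | 6.4% | 5.14 |
| 0.8 (assumed) | 5.6% | 5.92 |
| 0.9 (assumed) | 4.8% | 6.97 |

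**The case against.** The strongest reply is that this is a condensed article. It is silent on weights; it does not state that the analysis is unweighted, and a fuller plan may contain a participation analysis. That stands, so the point is about what section 3.6.2 describes and cannot be put as a decision against weighting.

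Three stronger readings are tempting, and the documents do not support them.

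- **That any link between attendance and glucose status biases the odds ratio by the same factor.** It does not. The factor is the ratio of the two groups' attendance ratios, and it cancels when they are equal. Attendance that depends on group alone, such as women with a GDM diagnosis being keener to come, also leaves the odds ratio unbiased.
- **That 21% is a response rate.** It is a recruitment target, produced partly by the quotas and by five of seven centers taking part. It does not measure self-selection, and no invitation or response counts are given.
- **That weighting would remove the shifts tabulated above.** Those assume selection on current glucose status, which is unknown for women who do not attend. Weights built on index-pregnancy data remove only the part that those data explain.

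It is also fair to say that the second adjustment step already conditions on pregnancy variables such as age, pre-pregnancy BMI, blood pressure and smoking. If selection runs through those variables and the model is right, the adjusted contrasts are protected. The prevalences are not. The variables named (as examples) do not include the GCT and OGTT values, which grade glycaemia within a group.

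On the quota mix, section 3.6.1 says the distribution over groups was based on BEDIP-N. If the two NGT groups really were equal in size in the cohort, the 50:50 mix would be harmless. The article gives no group sizes, so this cannot be confirmed. A normal-GCT share below one half would move the odds ratio the other way.

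**Conclusion.** The concern holds in limited form. Group prevalences are exposed whenever attendance depends on glycaemic risk within a group; odds ratios only when that dependence differs between groups. Under the plan's prevalences and an assumed r of 0.75 to 1.5 in the GDM group alone, 26% becomes 20.9% to 34.5% and the odds ratio of 2.58 becomes 1.93 to 3.86. These figures show sensitivity and do not estimate the bias, because the documents contain nothing on r.

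The quota effect on the pooled contrast follows from the design itself: 4.04 at 50:50, against 4.53 to 6.97 for an assumed normal-GCT share of 60% to 90%. Its size depends on a cohort share that the sponsor should know but the article does not give. The comparisons between single groups are not affected by the mix.

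This is a worthwhile and cheap improvement, not an error that invalidates the planned comparisons. That index-pregnancy data are held for women who do not attend is a reasonable inference (all 1800 had both tests, and a large pregnancy dataset is described), but it is not stated outright.

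**What to change.** 1. Among women of the five participating centers who consented to contact and were actually invited, tabulate participants against non-participants on index-pregnancy data (for example age, pre-pregnancy BMI, GCT and OGTT values, smoking, parity, center), by glucose tolerance group.
2. Within each group, model participation on those variables. Beside the planned models, report prevalences and group contrasts with inverse-probability-of-participation weights and robust standard errors, labelled as a sensitivity analysis.
3. Weight the pooled GDM versus non-GDM contrast to the cohort shares of the two NGT groups, and state those shares. The participation weights do not do this by themselves if invitations followed the quotas.

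The restriction to invited women matters: women at the two other centers could not take part, and women never invited must not be counted as refusers.

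**Cost.** Extra analysis on data reasonably inferred to be held, invitation records for each woman, and somewhat wider intervals in the weighted results. Two limits remain and should be stated: selection that index-pregnancy variables do not explain, and non-participants whose current eligibility (pregnancy, treatment, bariatric surgery) may be unknown.

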### 3.2. Recruitment and Eligibility

We aim to recruit 375 women–offspring pairs with the five largest centers who participated in the initial BEDIP study, which is approximately 21% of the initial 1800 women who received both a GCT and 75 g OGTT in the BEDIP study. Women and offspring are recruited according to three different subgroups based on the antenatal result of the GCT and OGTT in the index pregnancy (a sample of 125 in each group): GDM group; NGT on the OGTT with an abnormal preceding GCT (abnormal GCT-NGT group); NGT on the OGTT with a normal preceding GCT (normal GCT-NGT group). Abnormal GCT is defined as glucose ≥ 130 mg/dL, as we have previously shown to have an acceptable sensitivity to screen for GDM in our population (20). Additional analyses will be performed on the different subgroups stratified by a GCT ≥ 140 mg/dL to evaluate whether this leads to more pronounced differences in β-cell function and insulin sensitivity across the different groups. GDM was defined by the 2013 WHO criteria. Recruitment began in January 2021 and will end around December 2023.

Eligibility criteria:

The inclusion criteria for the mother are:Age ≥ 18 years;Participated in the completed BEDIP-N study and received both the GCT and the OGTT during pregnancy;

The inclusion criterion for the offspring is:Born at the time of participation in the BEDIP-N study.

The inclusion criterion for the father is:Biological father of the child born during participation in the BEDIP-N study.

The exclusion criteria for the mother are:Current pregnancy;Current treatment that influences glycemic status, such as high dose corticoids or incretin mimetic medication;History of bariatric surgery or any gastrointestinal surgery that alters glucose absorption (Billroth II);Inability to complete a normal study visit (incompliance, psychiatric problems);Diagnosis of type 1 diabetes or the presence of autoimmune antibodies for type 1 diabetes.

The exclusion criteria for the offspring are:Current treatment that influences glycemic status, such as high dose corticoids;Inability to complete a normal study visit (incompliance, psychiatric problems);Diagnosis of type 1 diabetes or the presence of autoimmune antibodies for type 1 diabetes.

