### 3.4. Outcomes of the Study

#### 3.4.1. Primary outcome

For mothers: A disorder of glucose metabolism: T2D defined by the 75 g OGTT and/or HbA1c, or prediabetes defined as IFG and/or IGT by the American Diabetes Association (ADA) criteria [1].

For offspring: BMI z-score as a continuous variable [23].

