### 3.5. Collection of Data from the Medical Electronical Records

For the mothers, we are collecting data concerning previous pregnancies other than the one during the BEDIP-N study. The following data are collected: pre-pregnancy weight, weight in early pregnancy, weight at delivery, pregnancy outcomes, gestational weight gain, parity, medical history, current treatment, history of metabolic syndrome, history of (pre)diabetes, diabetes related complications (retinopathy, microalbuminuria, nephropathy, neuropathy), cardiovascular diseases (heart, cerebral and peripheral arterial disease).

For the offspring, we will collect the following data from their medical records: medical history, current treatment, history of (pre)diabetes, information on school attendance (which school, which school year). Data on growth and weight trajectory, and data on the development of the child, will be collected through the databases used by the Flemish health services for the normal follow-up of children.

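### The maternal exclusion for treatment affecting glycemia, read as written, removes women drug-treated for T2D that is itself part of the primary outcome, so observed prevalence is too low

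*Protocol article*

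**What the plan says.** **Eligibility (3.2).** Mothers are excluded for "Current treatment that influences glycemic status, such as high dose corticoids or incretin mimetic medication". The matching criterion for the child gives only corticoids as an example; the maternal one adds a glucose-lowering class. The only diabetes excluded by diagnosis is type 1: "Diagnosis of type 1 diabetes or the presence of autoimmune antibodies for type 1 diabetes".

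**Primary outcome (3.4.1).** For mothers it is a disorder of glucose metabolism: "T2D defined by the 75 g OGTT and/or HbA1c, or prediabetes defined as IFG and/or IGT", by ADA criteria. Previously diagnosed or treated T2D is not mentioned. Section 2 puts the prevalence of T2D and prediabetes first among its objectives. There is one visit, three to seven years after delivery (3.3).

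**Records (3.5).** The items collected for mothers include "current treatment, history of metabolic syndrome, history of (pre)diabetes", together with diabetes complications. Nothing links them to the primary outcome.

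**Power (3.6.1).** For the GDM group (3) the text reads "where a 26% prevalence is assumed". The normal GCT-NGT (1) and abnormal GCT-NGT (2) groups are planned "with an assumed prevalence of 4% and 12%, respectively, with 125 subjects in each group". Stated power is 99% for 1 vs 3 and 81% for 2 vs 3, with no allowance for cases removed by the exclusion. Binary outcomes are reported as odds ratios (3.6.2).

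**The concern.** Any glucose-lowering drug influences glycemic status. Taken at its word, the criterion turns away a woman who developed T2D after the index pregnancy and takes medication for it, and it does so because she reached the endpoint. Such a woman belongs in the numerator of the prevalence that the study sets out to estimate. Losing her from both numerator and denominator lowers the estimate, and the loss falls on the severe end of the composite. Women with prediabetes or T2D who take no such drug are unaffected.

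Two results are at stake: the prevalence in each group, which is a stated objective, and the power of the 2 vs 3 comparison, which starts barely above 80%.

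**Working it through.** **Inputs.** Prevalences of 4%, 12% and 26%, n = 125 per group, chi-square test at 5% (3.6.1), taken as two-sided because sidedness is not stated. The share f of a group's cases that is excluded as already drug-treated is not in the documents; it is an assumption.

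**Step 1: the plan's own power.** With the pooled-variance normal approximation and no continuity correction,

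power = Φ{[|p3 − p2| − 1.96·√(2·p̄(1 − p̄)/n)] / √[(p3(1 − p3) + p2(1 − p2))/n]}.

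For 2 vs 3, p̄ = 0.19. The null standard error is √(2 × 0.19 × 0.81/125) = 0.0496 and the alternative one is √[(0.1924 + 0.1056)/125] = 0.0488. So power = Φ[(0.14 − 0.0973)/0.0488] = Φ(0.875) = 80.9%, against 81% stated. For 1 vs 3 the formula gives 99.9%, against 99% stated. The plan's figures reproduce.

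**Step 2: effect of the exclusion.** Removing a share f of cases changes prevalence p to

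p′ = p(1 − f)/(1 − pf).

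Example, GDM group with f = 5%: 0.26 × 0.95/(1 − 0.013) = 0.247/0.987 = 25.0%.

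The odds become p′/(1 − p′) = (1 − f) × p/(1 − p). The odds ratio for 3 vs 2 is therefore multiplied by (1 − f3)/(1 − f2). Equal shares cancel.

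**Step 3: results with 125 women still recruited per group.** The unaffected odds ratio is (0.26/0.74)/(0.12/0.88) = 2.58.

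| Assumed share of cases lost | GDM (3) | Abnormal GCT-NGT (2) | Risk difference, points | Odds ratio 3 vs 2 | Power 2 vs 3 |
|---|---|---|---|---|---|
| None | 26.0% | 12.0% | 14.0 | 2.58 | 80.9% |
| 5%, all groups | 25.0% | 11.5% | 13.6 | 2.58 | 79.6% |
| 10%, all groups | 24.0% | 10.9% | 13.1 | 2.58 | 78.2% |
| 20%, all groups | 21.9% | 9.8% | 12.1 | 2.58 | 74.8% |
| 5%, GDM only | 25.0% | 12.0% | 13.0 | 2.45 | 75.8% |
| 10%, GDM only | 24.0% | 12.0% | 12.0 | 2.32 | 69.9% |
| 20%, GDM only | 21.9% | 12.0% | 9.9 | 2.06 | 55.4% |
| 10% GDM, 20% other groups | 24.0% | 9.8% | 14.2 | 2.90 | 85.3% |

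Power for 1 vs 3 stays at or above 99% in both the all-groups and the GDM-only scenarios.

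**Step 4: which pattern is likely?** The introduction cites a seven-fold risk of T2D after GDM compared with normal glucose tolerance. The planned composite is 26% against (4% + 12%)/2 = 8% in the two comparison groups pooled, a ratio of 26/8 = 3.25. If both ratios applied here, T2D would make up a larger share of cases in the GDM group, and losses of treated T2D would be heavier there. The seven-fold figure comes from other populations, so this supports attenuation without proving it.

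**The case against.** **Treated T2D may not be meant.** The criterion names only high-dose corticoids and incretin mimetics. T2D is not an excluded diagnosis, and collecting diabetes history, treatment and complications suggests that women with established diabetes were expected. This stands in part. It shows that the intention is unclear, but the general wording still covers every glucose-lowering drug and has no exception, so a site that follows it will exclude these women.

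**A reader might infer that every group contrast is biased downward.** The documents do not support this. The planned measure is the odds ratio, which does not move under equal proportional loss and rises if the comparison groups lose the larger share. If only the GDM group loses cases, the 2 vs 1 contrast does not move at all.

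**A reader might take the lowest power figures as the expected loss.** They require up to 20% of GDM cases to be lost and none in the comparator. With 20% lost in all groups, power is 74.8%, not 55.4%. The calculation also treats the planning value of 26% as including treated women. Section 3.6.1 does not say so; if 26% already leaves them out, the stated power does not erode.

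**A reader might infer that a woman with known, controlled T2D who attends is scored as event-free.** Section 3.4.1 does not name known T2D as an event, but it does not say that it is disregarded either, and such coding may be set out in the full protocol or the analysis plan.

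**The exclusion has a purpose.** Treatment disturbs the OGTT-derived insulin-sensitivity and beta-cell indices (3.4.2). That justifies restricting those analyses. It does not justify removing the women from the primary outcome.

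**Conclusion.** The point holds as a conflict between eligibility and outcome. Read as written, section 3.2 selects on the maternal primary outcome and biases prevalence downward in every group that loses cases. Because eligibility and the primary outcome are both fixed in this article, this is more than omitted detail.

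The size is unknown. For an assumed 5% to 20% of cases lost, observed GDM prevalence is 25.0% to 21.9%. Power for 2 vs 3 is 79.6% to 74.8% if all groups lose that share, and 75.8% to 55.4% if only the GDM group does. The odds ratio stays at 2.58 in the first case and falls to 2.45 to 2.06 in the second. The direction of the bias in prevalence is certain if the criterion is applied literally. Attenuation of the odds ratio is plausible only, because it needs a larger share of cases lost in the GDM group. The power figures also assume that the 26% planning value includes treated women.

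**What to change.** 1. Reconcile sections 3.2, 3.4.1 and 3.5 so that treatment for T2D diagnosed since the index pregnancy does not by itself remove a woman from the primary-outcome analysis.
2. Count T2D documented in the record since the index pregnancy as a primary-outcome event, alongside the OGTT and HbA1c at the visit.
3. Restrict the OGTT-derived insulin-sensitivity and beta-cell indices to untreated women.
4. For women already screened out for this reason, report numbers by group where screening records allow, and add a sensitivity analysis that counts them as events.

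**Cost.** A short amendment to the eligibility wording and the outcome definition. For enrolled women the record data are already collected (3.5). A few women will contribute to the primary outcome but not to the OGTT-derived indices. The record data do not cover women who were turned away, and the article describes no screening log. Since recruitment began in January 2021 and was to end around December 2023, those women may be only partly recoverable.
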